## 7. Objectives

### 7.1. Primary

The principal objective of the CONFIDENT trial is to assess the efficacy of 2 units (400-500mL) of plasma collected in convalescents of COVID-19 infection with a titer greater or equal to 1/320 (plaque reduction neutralization test 50) neutralizing antibodies against SARS-CoV-2 with the standard of care, as compared to standard of care, to reduce the mortality at day 28 after inclusion of the patients with SARS-CoV-2 pneumonia who require mechanical ventilation. In case of shortage of plasma with a titer greater or equal to 1/320 on the moment of patient enrolment, plasma from convalescent donors with a titer of at least 1/80 will be released for transfusion. The standard of care will be made of therapies currently recommended in international guidelines regarding organ failure support and treatment of secondary events. At the present time, no treatment is directed against SARS-CoV-2 or the inflammatory response characteristic of this specific disease. In case of evolution of the guidelines due to new scientific release during the study period, the standard of care will be adapted in the two treatment groups.

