## 8. Background Information and Scientific Rationale

The COVID-19 pandemic started in China in December 2019 and spread to European countries in early 2020, affecting most severely Italy, Spain and France. Belgium was affected during the same wave and first deaths due to COVID-19 were reported in early March 2020. As of September 10, 2020, almost 28 million cases, including 900,000 deaths, have been confirmed over the world and almost 90,000 cases, including 9,900 deaths, have been declared in Belgium [10].

Current data from the Belgian surveillance system indicate that 20% of the hospitalized patients are in ICUs [11]. Hospital deaths occur either in the ICU (13 / 31, 31 % in Liège University Hospital, personal data) or in non-ICU wards for those patients who would not benefit from intensive care as anticipated by the medical team [12]. Based on United Kingdom ICNARC reports, and according to personal observations in Belgium, the COVID-19 ICU patients require mechanical ventilation in 60% of cases, particularly when they are referred directly by the emergency medical service. According to different series, forty to sixty percent of the mechanically ventilated patients are likely to die, most of them when mechanical ventilation is instituted early (30% survival rate) rather than late in the course of the disease (70 % survival rate) [13]. Similar observations have been made in China [14]. Besides the direct cost in human lives, the current situation in European countries has led to a halt in most of medical and scheduled surgical practices for non COVID-19 patients and to a doubling of the number of ICU beds. The nursing and medical manpower per patient in ICUs has also been doubled due to the intensity of care that patients require with the use of invasive ventilation and the practice of alternate prone positioning for severe ARDS [15].

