## 9.9. Statistical Analysis

- Primary outcome

The primary outcome of the trial is mortality at day 28. Based on prior reports from China, Italy and UK, and consistent with personal observations, we anticipate that the mortality at day 28 will be around 40 %. As no comparative study has yet been published, the reduction that we anticipate is empiric. We consider that a one third relative reduction in 28-day mortality is realistic and clinically relevant. As this reduction might be greater, we plan to perform an interim analysis for ethical reasons. With a two-sided  $\alpha$ -risk of 0.05 and a  $\beta$ -risk of 0.20, the minimal number of patients to include to reach significance for a one third relative reduction in 28-day mortality (an absolute reduction of 13.5% day-28 mortality in the intervention group assuming a day-28 mortality of 40 % in the control group) is 250 in the control group and 250 in the active group (total number of patients = 500). This number allows for four interim analyses to be performed in addition to the final analysis, respectively after assessment of 100, 200, 300, 400 and 500 patients. Considering that others trials in COVID-19 may result in modification in mortality and therefore in standard of care, we anticipate that the number of patients that is necessary to address our hypothesis may vary, and will have to be adapted depending on the results of the interim analyses.

- Statistical analysis plan

Results will be analysed in intention to treat and expressed as means and standard deviations (SD) for quantitative variables with a Normal distribution and as medians and 25th to 75th percentiles for skewed distributed quantitative variables. Qualitative variables will be expressed using counts and percentages.

Mean values between groups will be compared by Student t-test but also by the non-parametric Wilcoxon test when normality assumption is not fulfilled. Proportions will be compared by the chi-square

test. Appropriate multivariate analyses will be performed to assess the relationship between outcome and patients' characteristics and clinical features.

For the primary endpoints, vital status at day 28 in all groups will be calculated with corresponding 95% CI. Comparison between groups will be tested using chi-square test.

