Regarding the secondary endpoints, quantitative values between groups will be compared by Student t-test or non-parametric Wilcoxon for the SOFA score (at different time points), viral load of SARS-CoV-2 (at different time points), circulating CRP (at different time points), ADL score at day 90, anxiety-depression scale at day 90, sero-conversion. Poisson regression analysis will be considered to analyse number of ventilator-free days up to day 28. Comparison of proportions will be applied to compare location of patient at day 90, as well as presence of various adverse events. If descriptive analysis revealed the presence of potential confounding factors, appropriate multivariate analysis will then be considered.

The two-sided level of significance used in this trial is 5%. Statistical analyses will be carried out using SAS (version 9.4 for Windows) statistical package.

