The interim analyses will be performed with 100, 200, 300 and 400 patients evaluable for 28-day mortality. Two Lan-Demets spending functions will be used: one, similar to a Pocock (aggressive) boundary to stop the study for futility, and the other, similar to an O'Brien-Fleming (conservative) boundary to stop the study for extreme efficacy. If the interim analyses take place with increments of exactly 100 patients, and assuming a mortality of 40% in the control group, the recommendations to stop the study for futility or for efficacy are summarized in Table 2. Of note, the trial will reach statistical significance if the absolute difference in 28-day mortality is 9% or larger, which might still be a clinically worthwhile difference. The rules for DSMB recommendations shown in Table 2 will not be binding.

**Table 2:** interim analyses and potential recommendations of the DSMB to stop the trial for futility or efficacy, depending on the observed treatment effect (and associated P-value)

| Interim analysis | Number of patients | Recommend stopping for futility if difference in mortality is smaller than | Recommend stopping for efficacy if difference in mortality is greater than |
|------------------|--------------------|----------------------------------------------------------------------------|----------------------------------------------------------------------------|
| 1                | 100                | 0.02 ( $P > 0.83$ )                                                        | -                                                                          |
| 2                | 200                | 0.04 ( $P > 0.60$ )                                                        | 0.22 ( $P < 0.001$ )                                                       |
| 3                | 300                | 0.06 ( $P > 0.28$ )                                                        | 0.14 ( $P < 0.007$ )                                                       |
| 4                | 400                | 0.08 ( $P > 0.12$ )                                                        | 0.11 ( $P < 0.022$ )                                                       |
| 5 (final)        | 500                | -                                                                          | 0.09 ( $P < 0.042$ )                                                       |

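### Table 2 prints each stopping limit as a mortality difference and as a P-value; the two can disagree, even at 40% control mortality, and section 9.9 does not say which governs

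*Protocol*

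**What the plan says.** Section 9.9 of the protocol (Interim analysis plan) sets looks at 100, 200, 300 and 400 patients before the final analysis at 500. Lan-DeMets spending functions define the limits: Pocock-like for futility and O'Brien-Fleming-like for efficacy. The limits hold for looks at exact increments of 100. The further condition on mortality reads: "assuming a mortality of 40% in the control group, the recommendations to stop the study for futility or for efficacy are summarized in Table 2". Each limit is a difference with a P-value in brackets:

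- Futility: 0.02 (P>0.83), 0.04 (P>0.60), 0.06 (P>0.28), 0.08 (P>0.12).
- Efficacy, from the second look: 0.22 (P<0.001), 0.14 (P<0.007), 0.11 (P<0.022), 0.09 (P<0.042).

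The text then says that "the trial will reach statistical significance if the absolute difference in 28-day mortality is 9% or larger", without repeating the 40% condition. The DSMB rules are described as non-binding. The primary test is the chi-square test.

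The trial is sized for a relative effect, a one-third reduction, stated as "an absolute reduction of 13.5% day-28 mortality in the intervention group assuming a day-28 mortality of 40 % in the control group". The control rate may move. Section 7.1 says: "In case of evolution of the guidelines due to new scientific release during the study period, the standard of care will be adapted". Section 9.9 adds: "Considering that others trials in COVID-19 may result in modification in mortality and therefore in standard of care", and expects the number of patients to be adapted at the interim analyses.

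**The concern.** A fixed absolute difference corresponds to one P-value only at one control mortality. Away from that rate, the two halves of a Table 2 cell become different rules. The protocol foresees that the rate may move, gives the difference the leading place in the table, and states no order of precedence. A DSMB or final analysis that reads the difference column could stop for futility, or withhold a claim of benefit, when the spending boundary says otherwise. At higher mortality it could claim benefit slightly too easily. A decision threshold should have one reading.

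**Working it through.** **Inputs.** From section 9.9: 250 per arm, equal looks of 50 per arm, two-sided 5%, chi-square test, and the Table 2 limits. Assumptions of this check: 30% or 50% control mortality, and the one-third reduction carrying over to 30%.

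**1. Reproducing the plan's P limits.** A Lan-DeMets O'Brien-Fleming-type boundary (two-sided 0.05, five equal looks, 4 million simulated paths) gives nominal P of 0.0008, 0.0075, 0.0222 and 0.0423 at looks 2 to 5. The plan prints 0.001, 0.007, 0.022 and 0.042. The efficacy P limits are therefore the spending boundary, which does not depend on control mortality.

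**2. Converting between the scales at 40% control.** With n per arm and pooled proportion p̄, z = (p_C − p_T) / √(2p̄(1−p̄)/n).

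| Patients | Printed pair | P at the printed difference | Difference at the printed P |
|---|---|---|---|
| 100, futility | 0.02, P>0.83 | 0.838 | 0.021 |
| 200, futility | 0.04, P>0.60 | 0.560 | 0.036 |
| 300, futility | 0.06, P>0.28 | 0.282 | 0.060 |
| 400, futility | 0.08, P>0.12 | 0.096 | 0.075 |
| 200, efficacy | 0.22, P<0.001 | 0.0006 | 0.212 |
| 300, efficacy | 0.14, P<0.007 | 0.0099 | 0.146 |
| 400, efficacy | 0.11, P<0.022 | 0.0207 | 0.109 |
| 500, efficacy | 0.09, P<0.042 | 0.0355 | 0.087 |

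Most pairs agree to rounding. The 300-patient efficacy pair does not, and the 400-patient futility pair is loose.

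**3. Worked results.**
- 300 patients, 60/150 versus 39/150: p̄ = 99/300 = 0.33; z = 0.14/0.0543 = 2.58; P = 0.0099, not below 0.007.
- 400 patients, 80/200 versus 65/200: p̄ = 0.3625; z = 0.075/0.0481 = 1.56; P = 0.119. The difference says stop (below 0.08); the P limit says continue (not above 0.12).
- 400 patients at 30% control, 60/200 versus 46/200: 0.070, z = 0.070/0.0441 = 1.59, P = 0.113. The same conflict, wider.
- Final at 30% control, 75/250 versus 54/250: 0.084, z = 0.084/0.0391 = 2.15, P = 0.032. Inside P<0.042, but short of 0.09. At 30% control, P = 0.042 corresponds to 0.080.

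**4. Operating characteristics.** 1,000,000 simulated trials per scenario, 50 per arm per stage, benefit direction only. A result equal to an efficacy limit counts as crossing it.

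| Control vs plasma | Futility | Difference limits | P limits |
|---|---|---|---|
| 30% vs 20% | obeyed | 53.7% | 60.8% |
| 30% vs 20% | ignored | 62.4% | 72.5% |
| 35% vs 23.3% | obeyed | 66.7% | 69.5% |
| 35% vs 23.3% | ignored | 76.4% | 81.2% |
| 40% vs 26.7% | obeyed | 77.0% | 76.8% |
| 40% vs 26.7% | ignored | 86.3% | 88.0% |
| 30% vs 30% (error) | ignored | 1.9% | 2.5% |
| 40% vs 40% (error) | ignored | 2.75% | 2.5% |
| 50% vs 50% (error) | ignored | 3.0% | 2.6% |

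The one-sided target is 2.5%, half of the two-sided 5%.

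**5. The 9% sentence.** With 250 per arm, 9 points is 22.5 deaths, so the smallest attainable difference that meets it is 23/250 = 0.092. Over all mortality levels the largest P at that difference is 0.0397, which is below 0.042.

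**The case against.** The natural reading of section 9.9 already favours the P-values. The spending functions are named first, Table 2 follows as a case worked at 40%, every limit carries its P-value, the primary test is chi-square, and the rules are non-binding. This stands, and it is why the point is about precedence and not about a wrong design. It does not close the gap. No sentence says that the differences are illustrative, and the table headings put the rule in terms of the difference.

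A reader might infer that the plan itself loses 7 to 10 points of power. The documents do not support that. The loss needs three things that they do not state: control mortality of 30%, the one-third effect carried over to it, and the differences followed in place of the P limits. Section 8 reports that "forty to sixty percent of the mechanically ventilated patients are likely to die", so mortality could equally be above 40%, where the mismatch reverses. The figures also hold the size at 500, although section 9.9 allows adaptation. Nor do the documents say that standard of care will change; both statements are conditional.

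A reader might also infer that the 9% sentence is false, or that it declares smaller significant differences non-significant. It says if, not only if, and step 5 shows that it holds at any mortality.

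Finally, Table 2 says greater than. On a strict reading with exactly 150 per arm, 0.14 itself does not cross. The next attainable difference, 22/150 = 0.147 (60 versus 38 deaths), has P=0.0068 and meets both limits. Repeating the simulation strictly gives an error of about 2.5% at 40% control and 2.7% at 50%. So the excess error at 40% depends on how a tie is treated. The mismatch of the printed pair and the 400-patient futility conflict do not.

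**Conclusion.** The point holds as a defect in how the decision rule is stated. Table 2 gives two criteria per cell without precedence, and they can give opposite advice on ordinary data. At 40% control mortality the conflict is small: futility at 400 patients, and an efficacy difference at 300 patients that does not match its P-value. Followed alone with futility ignored, and with ties counted as crossing, the differences give a one-sided error of about 2.75% at 40% control and 3.0% at 50%.

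Under the assumed fall to 30% with a one-third reduction, following the differences instead of the P limits would lower power from about 61% to 54% (futility obeyed) or from 72% to 62% (futility ignored). At 35% the cost is about 3 to 5 points. These are consequences of one reading, not properties of the plan. Separately, power under the P limits falls from 88% at 40% versus 26.7% to 72.5% at 30% versus 20% (futility ignored). That fall comes from the lower event rate and is not part of this point.

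The 9% sentence is true but incomplete as a criterion, because smaller differences can also reach P<0.042: about 8 points at 30% control.

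**What to change.** In section 9.9:

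- State that the Lan-DeMets boundary on the test statistic (Z or P, in the direction of benefit) governs at every look and at the final analysis.
- Label the Table 2 differences as approximate illustrations at 40% control mortality.
- Correct the 300-patient efficacy difference to about 0.15 (0.146 to three decimals). Recheck the 400-patient futility difference, where P=0.12 corresponds to 0.075.
- Add to the 9% sentence: *at 40% control mortality; the criterion is P<0.042*.

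The DSMB charter should carry the same wording. The cost is a few lines of text; sample size, timing of looks and spending functions do not change.

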## 9.10. Changes in the Conduct of the Study or Planned Analyses

- Provision for adaptive design changes at the time of interim analyses

Because of the considerable uncertainties about the outcomes that will be observed in the three arms of the trial, the DSMB will be allowed to recommend design changes based on the observed data at the times of the interim analyses. These changes may include an adaptation of the sample size or the patient selection. Any such changes are adaptive in nature and will be implemented using appropriate methods to control the impact of these changes on the operating characteristics of the trial (especially the probability of type I error).

### **9.11. Protocol Amendments**

If amendments to the protocol (modifying sense or objectives or modifying the undergone constraints or the risks incurred by the subjects) turn out to be necessary, they will be submitted to the opinion of the EC having examined the initial protocol.

## 10. Study patients

### 10.1. Disposition of patient

- Clear accounting of all patients who entered the study (e.g. randomized, completed the study, screened, discontinued, ...)
- Give reasons for discontinuation
- State whether blind was broken

### 10.2. Protocol Deviations

All deviations related to study inclusion or exclusion criteria, conduct of the trial, patient management or patient assessment should be described.

### 10.3. Data Management Responsibilities

The study will be monitored by a DSMB that will include international members not involved in this protocol and a statistician. The DSMB will review the safety data at least every 6 months and at each interim analysis.

### 10.4. Study Data, Data Ownership and Data Sharing with KCE

After the completion of the study the Sponsor will transfer the pseudonymized study data set to KCE. KCE will request approval from the competent chamber of the Information Security Committee to have the relevant study data linked with IMA data by a trusted third party (TTP, eHealth platform) using the patient national number.

The patient information and consent includes wording that the **national number** will be recorded on site by the investigator for later data linkage. The patient information and consent will also include that in case the patient is randomized, it is planned that a trusted third party (TTP, eHealth platform) will receive and use the national number to link with IMA administrative data. This data linkage is planned to obtain a more complete data set that will be used for the analysis of effectiveness and cost-effectiveness of the intervention by KCE.

KCE and Sponsor have entered into a research agreement detailing the roles and responsibilities of each party, as well as other legal aspects of this collaboration, including the right to use and access of KCE to the Study Data.

“Background” means any intellectual property (IP), data, materials, information owned or controlled by the Sponsor or a Site, and required to run this Study. Sponsor will identify such Background including the legal restrictions of which Sponsor or Sites are aware that may affect the use of the Background for the purpose of the Study or the rights granted to KCE under this Agreement.

The Study Data consist of this protocol, including amendments, the electronic forms for data capture, including the annotations and guidance for use, the electronic database of the pseudonymized clinical and non-clinical data collected using data capture, including the log of changes from data entry to

database lock, study reports based on these pseudonymized data, and any data or reports generated at a later stage, eg based on exploratory analyses or stored samples.

“Foreground” means any Study Data, and any tangible biological, chemical and physical material and inventions, that are generated, acquired, discovered, conceived, developed, created, exemplified or derived as a result of carrying out the Clinical Study, whatever its form or nature, whether it can be protected or not, as well as any Foreground IP. Sponsor acknowledges that the main purpose of the research performed under this Agreement is to generate results that will serve the general public interests, and specifically the interests of the patients and public healthcare decision making bodies, and, therefore, undertakes not to exploit the Foreground in any way that is or could be detrimental to such interests.

The Sponsor owns the Study Data, but provides KCE with a copy of the pseudonymized database after database lock as well as a royalty-free unrestricted license to use the Study Data for non-commercial public health related purposes as detailed in the Agreement between KCE and Sponsor. If judged appropriate, KCE will introduce the request to the competent chamber of the Information Security Committee and arrange for the data linkage. For the sake of clarity, the linked data are not part of the Study Data. However, KCE will discuss with the Sponsor the results of the analyses and the reporting of the linked data.

## 11. Finance and Insurance

- Insurance without fault (Law of 7 May 2004) : Ethias Insurance

According to the Belgian law, the principal investigator is responsible for any damage, even without fault, caused directly or indirectly to the participant by the experimentation. Therefore, a specific trial insurance will be provided for patients treated in Belgium through the CHU of Liège.

- The financial agreement between the promotor, the investigator and the Institution, incorporates:
  - Data protection
  - Conflict of interests

## 12. Dissemination of Results and Publication Policy

The results will be submitted for presentation to international societies of critical care and/or infectious diseases and for publication to an international scientific medical journal. The authorship will include the members of the writing and/or steering committee, the investigators from centers having recruited at least 10 patients, a representative of the Belgian Red Cross and transfusion services, the biostatistician of the study and all scientists whose contribution will have been substantial. Pseudonymised Data from this study can be used by the funder (KCE) (for more details, please check the research agreement signed between sponsor and KCE) or similar public healthcare research institutes in Europe for further analyses, for example to determine whether one of the treatments studied provides better value in meta-analyses.

The data required by the European requirements will be shared according to [https://ec.europa.eu/health/blood\\_tissues\\_organs/covid-19\\_en](https://ec.europa.eu/health/blood_tissues_organs/covid-19_en), and the trial will be registered at [https://ec.europa.eu/health/sites/health/files/blood\\_tissues\\_organs/docs/guidance\\_plasma\\_covid19\\_en.pdf](https://ec.europa.eu/health/sites/health/files/blood_tissues_organs/docs/guidance_plasma_covid19_en.pdf).

